**Fig. 1 Fig1:**
[figure not shown]
Study Schema

### Sample size and power considerations

As this study is interested in non-inferiority, all statistical tests were one-tailed with an alpha of 0.025 to address type 1 error. At time of protocol development, there were 97 eligible ACs. We assumed 10% of the ACs were would not participate in the study leaving 87 ACs eligible for randomization (approximately 43 per arm), with a total of 1986 participants (993 per arm). We proposed a clustered sampling strategy for our study. There is a paucity of information in the literature regarding correlation between individuals within ACs, therefore we reviewed the literature relating to the clustering effect of facilities. Thus, to account for the correlation within clusters we assumed a correlation ranging from 0.05–0.10 and an average cluster size of 24 [23, 24] resulting in our estimated design effect (deff) ranging from 2.15–3.3. We applied the deff to our total sample size to determine the effective sample size. Assuming retention in care would range from 75 to 85% with a 10% difference in retention in care between the control and intervention groups, we estimated the power of our study to range from 0.80–0.98. See supplementary materials for detailed sample size calculations.

### Primary outcome measures

Primary outcomes are retention in Ubuntu clinic care (AC or clinic care), retention in AC care, annual viral load completion rates, and VL suppression (VL < 400 copies/ml).

### Secondary outcome measures

#### Medicine supply chain feasibility measures

Patient related:number of study participants whose regimen was switched during the study (including date of switch);number of study participants reporting ART medicine losses and the reported reason for such losses including, but not limited to, theft, damage or destruction in the home or unauthorized loan or provision to another person who ran out of ART;number of study participants requests for additional ART refill supply from the clinic pharmacy in between AC visits and the reasons for such requests.System related:number of short supplies due to medicine supply shortages, supply chain gaps and expiry date related losses;medicines quantities wasted due to any of: expiry, re-issue, regimen switch, non-collection or any other reason.

#### Clinic patient congestion impact measures

Number of clinic visits per annum (AC and non-AC visits) for intervention arm and SOC Arm.

### Data collection

Following recruitment, ACs that are eligible, consent, and are randomized to the intervention arm will be transitioned to Intervention ACs. Duration of follow-up for patients is identical for patients in both arms of the studies.

Primary outcome data will be extracted from routine clinical records including AC registers, the National Health Laboratory Services, and patient paper and electronic records. Data will be collected for 27 months: 24 from the start of the study, with three additional months of follow-up before closing the dataset to ascertain final outcomes. This will be supplemented by data from the Western Cape provincial health data center, which uses probabilistic matching algorithms to link patient data from different Western Cape facilities, laboratory systems and pharmacy data.

Secondary outcome data related to medicine supply chain feasibility will be collected by the study team in collaboration with the pharmacy staff at the study site onto a lost drug reporting form, and will be compiled in a study database.

Additional data on ART dispensing between study visits and secondary outcome data related to patient visit data will be extracted from the provincial health data system.

Collection of participant names and other identifiers will be restricted to informed consent documents, and a study identification key, all of which will be kept in a locked cabinet in the study office at MSF separate from other study documentation and accessible only by the MSF project coordinator and PI. These records will be destroyed 3 years after completion of the final study report by a company that destroys confidential patient documents. All electronic records will be kept in password-protected files. All electronic communications of study data will be through password-protected, encrypted files.

### Data analysis

#### Primary outcomes

Analysis will be completed using STATA 14 [22] and will include: descriptive summary statistics of baseline patient characteristics, Kaplan-Meier estimates of time to loss to follow-up and first unsuppressed viral load, and calculation of the risk and hazards ratios at 12 and 24 months.

“Retention in care” will be defined as the proportion of patients retained in ART care at Ubuntu Clinic, in or out of an AC. If a patient transferred out of Ubuntu clinic before 24 months, he/she will be excluded from the denominator. “Retention in club care” will be defined as remaining a member of the original study AC at 24 months. If a patient leaves transferred out of their AC before 24 months, he/she is excluded from the denominator.

“Lost to follow up” is defined as patients failing to return to clinic or AC care for 3 months after a missed visit. “Viral load completion” is defined as having a viral load drawn within the first and second 12 month period after study start. If a patient is lost to follow-up, transferred out of clinic, or dies they are excluded from the denominator. “Viral load suppression” is defined as < 400 copies/mL. Only those patients with a completed viral load and retained in care at 24 months, are included in the denominator for viral load suppression. Patients who die or who are transferred out will be censored at the date of this outcome.

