#### The intervention ACs

The Intervention ACs meet twice annually receiving six-month ART refills, with the patient being asked to individually attend a third visit for routine blood collection anytime two-four weeks before their annual clinical assessment AC visit. Patients in Intervention ACs are not able to send a treatment “buddy” to collect their ART refill to ensure the health system interacts with patient at least twice a year.

In both SOC and Intervention ACs, a five-day grace period is permitted for late attendance. In other words, AC patients need to come within 1 week of their AC visit to collect their ART refill or they are up-referred to the clinician-led ART care based at the clinic. A patient is also up-referred if they experience viral rebound (a viral load of > 400 copies/mL) or develop another clinical condition that requires more regular clinical support (Table 2).

**Table 2 Tab2:** Comparison of SOC ACs and Intervention ACs

	Standard of Care ACs	Intervention six-month ACs
Frequency of AC visits	2-monthly (5 per year)	6-monthly (2 per year)
ART dispensing interval	2-monthly (5 per year)	6-monthly (2 per year)
Frequency of clinical assessments	12-monthly	12-monthly
Frequency of routine bloods	12-monthly	12-monthly
Timing of routine bloods	As part of AC visit	As an additional individual visit, 2–4 weeks before clinical assessment AC visit
Units of care	Groups of 25–30	Groups of 25–30
Peer-based support	Strong emphasis	Strong emphasis
Patient self-management	Strong emphasis	Strong emphasis
Management of clinical complications	Up-referral to clinician-led ART care based at the clinic	Up-referral to clinician-led ART care based at the clinic
ART packing and dispensing	Pre-packed by central dispensing unit, supplied to clinic pharmacy and dispensed at AC visit	Pre-packed at clinic pharmacy with support from study team staff and dispensed at AC visit
Treatment “buddies”*	Allowed to collect at every alternate AC visit	Not permitted
Standard number of contacts per year	5 (all within the AC)	3 (2 within the AC and 1 individual for routine bloods)
Minimum number of contacts per year	3 (could send a “treatment buddy” to collect ART twice)	3 (within the AC and 1 for routine bloods)

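### The denominator rule for club retention, one of the primary outcomes, is garbled and as worded removes patients who leave the club, so a difference that runs through up-referral can disappear

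*Protocol article*

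**What the plan says.** Under *Primary outcome measures* the article states: "Primary outcomes are retention in Ubuntu clinic care (AC or clinic care), retention in AC care, annual viral load completion rates, and VL suppression". Club retention is therefore primary in its own right, beside clinic retention.

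The definitions are under *Data analysis, Primary outcomes*. Club retention "will be defined as remaining a member of the original study AC at 24 months". The denominator rule follows at once: "If a patient leaves transferred out of their AC before 24 months, he/she is excluded from the denominator". Two neighbouring rules help in reading it:

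- Clinic retention, which counts patients whether or not they are still in a club: "If a patient transferred out of Ubuntu clinic before 24 months, he/she will be excluded from the denominator".
- Viral load completion: "If a patient is lost to follow-up, transferred out of clinic, or dies they are excluded from the denominator".

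*The intervention ACs* describes how patients in both arms come to leave a club. The rule for late collection is: "AC patients need to come within 1 week of their AC visit to collect their ART refill or they are up-referred to the clinician-led ART" (meaning the clinic's own service). Viral rebound, or a condition needing closer clinical support, has the same result.

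**The concern.** If success means still belonging to the club, failure means no longer belonging to it. A rule that drops people because they left the club makes the denominator depend on the outcome. Up-referral is the route out of the club that the protocol itself describes, so it would probably account for many of the dropped patients.

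The exclusion need not be neutral between arms. The standard-of-care clubs have five collections a year and allow a treatment buddy at alternate visits. The intervention clubs have two collections and no buddies. The documents do not show which arm will have more exits. Whichever it is, deleting the exits hides the difference. If the intervention arm has more, the deletion favours non-inferiority. If it has fewer, a benefit is hidden.

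Clinic retention does not fill the gap, because an up-referred patient who stays at Ubuntu clinic is a success there. The interim review by the Data Monitoring Committee also looks at the primary outcomes for evidence of inferiority, so the same rule, if applied at 12 months, would affect that review.

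**Working it through.** **The plan's own figure.** *Sample size and power considerations* gives 993 per arm, cluster size 24, intracluster correlation 0.05–0.10, one-sided alpha 0.025, retention 75–85%, a 10% difference and power 0.80–0.98.

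- Design effect = 1 + (24 − 1) × 0.05 = 2.15, and 1 + 23 × 0.10 = 3.30. Both match the article.
- Effective n per arm = 993/2.15 = 461.9, and 993/3.30 = 300.9.
- Power = Φ(0.10/√(2p(1−p)/n) − 1.96), taking 10 points as the margin and a true difference of zero. With p = 0.75 and n = 300.9 this is 0.809. With p = 0.85 and n = 461.9 it is 0.989.

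This agrees with the stated range to about one point. The 10-point margin is thus an inference. The article does not call it a margin, and it states it for retention in care, not for club retention. It is used below only as a yardstick.

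**Assumed outcomes.** The documents give no split of exits, so these are assumptions:

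- Standard of care: 80% stay in the club (S), 7% up-referred (U), 5% transferred to another facility (T), 7% lost (L), 1% dead (D).
- Intervention: 68% stay, a true deficit of 12 points. The extra 12 points fall either on up-referral (19% against 7%) or on loss (19% against 7%).

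**Formulas.** Observed retention is S divided by the share left in the denominator. Non-inferiority (NI) is declared when the lower bound d − 1.96·SE lies above −10 points. Here SE = √(deff × [p₁(1−p₁)/n₁ + p₂(1−p₂)/n₂]), with 993 per arm before exclusions and deff 2.15 to 3.30.

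| Denominator | Deficit through up-referral | Deficit through loss |
|---|---|---|
| Everyone | 80.0% v 68.0%; NI declared in 0.4–0.6% of trials | the same |
| Drops T only | 80/95 = 84.2% v 68/95 = 71.6%; 0.2–0.3% | the same |
| Drops T and U | 80/88 = 90.9% v 68/76 = 89.5%; 89–98% | 80/88 = 90.9% v 68/88 = 77.3%; under 0.1% |
| Drops T, U and L | 80/81 = 98.8% v 68/69 = 98.6%; about 100% | the same |

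In the third row, the up-referral deficit shows as 1.4 points with a lower bound of −5.7 to −6.7. With everyone in the denominator, the bound is −17.6 to −18.9.

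**Range of deficits through up-referral.** Keep T at 5% and L + D at 8% in both arms, and drop T and U. The observed intervention rate is then S/(S + 8):

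- S = 75: 75/83 = 90.4%, so a true 5-point deficit shows as 0.5.
- S = 68: 68/76 = 89.5%, so 12 points show as 1.4.
- S = 60: 60/68 = 88.2%, so 20 points show as 2.7.

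**Does clinic retention catch it?** If up-referred patients stay at the clinic, clinic retention is (S + U)/(100 − T). A deficit through up-referral gives 87/95 = 91.6% in both arms, so it is invisible. A deficit through loss gives 87/95 = 91.6% against 75/95 = 78.9%, so it is visible.

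**The case against.** The strongest reply is that the sentence is a drafting remnant meant to exclude administrative transfers only, in parallel with the clinic-retention rule. The article has its own term, up-referral, for exits after late collection or rebound, and elsewhere uses transfer for moving to another club. On that reading up-referrals stay as failures and the second row of the table applies, with nothing hidden. The reading is possible but strained. The rule concerns moves out of the AC rather than out of the clinic, and it contains the verb for leaving. A primary outcome should not depend on which half of a garbled sentence the analyst keeps.

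A reader might go further and infer that non-inferiority on this outcome is close to guaranteed. The documents do not support that. The viral load completion rule names loss and death separately from transfer, while the club rule does not. Lost and deceased patients therefore appear to remain as failures, and a deficit through loss would be seen. The extreme fourth row needs lost patients to count as leavers too. That cannot be ruled out, since up-referral for a missed collection precedes the three-month definition of loss, but it is not what the text says.

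Nor does the point undermine the whole trial. It concerns one of four primary outcomes. The sentence does not touch clinic retention, and the planned analysis of time to first unsuppressed viral load can register the rebound that leads to up-referral. That analysis does not register up-referral for late collection.

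**Conclusion.** The point stands in a limited form. As worded, the rule conditions the denominator of a primary outcome on the event the outcome is meant to count, and it can conceal a difference in club exits through up-referral. In the illustration a 12-point deficit shrinks to about 1.4 points, and the chance of declaring non-inferiority rises from under 1% to 89–98%. This rests on three assumptions: that leaving or transferring out of the club includes up-referral, that the deficit runs through that route, and that a 10-point margin applies to this outcome. The splits are invented for illustration and do not predict what the trial will find. The sentence should be corrected before the 24-month analysis.

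**What to change.** Replace the exclusion with a fixed denominator of all participants in the randomised AC. Count every exit from the original AC as not retained in club care, and name up-referral and loss to follow-up explicitly. State how deaths and administrative transfers, such as relocation to another facility, are handled in the main analysis, and add a sensitivity analysis that treats them the other way. Counting them as failures is one defensible choice among several. What matters is that the choice is stated and made before the data are analysed.

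The cost is a few sentences. Membership at 24 months is already needed for the numerator, and deaths and transfers are already needed for the other outcome rules, so no new data source appears necessary. The article names AC registers as a source but does not say whether they record reasons for exit, so this should be confirmed for the sensitivity analysis. The downside is that reported club retention will be lower.

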#### The SOC ACs

Participants in the SoC ACs will continue to be provided with their ART refill, clinical care and support following the current Western Cape provincial AC guidelines. At time of protocol submission, SOC ACs were groups of 25–30 stable patients who had been on ART for 6 months or more, had an undetectable viral load, and were referred by a clinician to the model of care. SOC ACs are facilitated by a lay healthcare worker and meet five times per year (bi-monthly with a four-month gap over the end of the year to support migration patterns) for a group support session, a brief symptom check and distribution of pre-packed ART with referral by the lay provider to a nurse based at the clinic if necessary. At one of these visits the patient’s blood is taken by a nurse for routine blood monitoring, including viral load. At the following AC visit, each AC member has their annual clinical assessment with a nurse.

Patients are allowed to send a treatment “buddy” to collect their ART refill to every alternate AC. A treatment buddy is a friend or family member of an AC member requested by the AC member to collect their ART refill at from the AC on the AC member’s behalf.

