### Interim analyses

12-month primary outcomes will be assessed. An independent Data Monitoring Committee will conduct an interim review of the study patient primary outcomes. Should there be evidence of inferiority, it will be in a position to recommend stopping the study early (and disseminating study findings rapidly).

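### Loss to follow-up is triggered by a missed scheduled visit, and visit frequency is the randomised factor, so time to loss and its hazard ratio are measured differently in the two arms

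*Protocol article*

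**What the plan says.** All references are to the protocol article.

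- **Loss rule (Data analysis, Primary outcomes).** Lost to follow-up "is defined as patients failing to return to clinic or AC care for 3 months after a missed visit". The wording is the same for both arms. Deaths and transfers are censored at their own date, but no date is assigned to loss.
- **Use of the rule (same section).** The analysis includes "Kaplan-Meier estimates of time to loss to follow-up and first unsuppressed viral load", with risk and hazard ratios at 12 and 24 months. Participants recorded as lost also leave the viral load completion denominator.
- **Retention (same section).** Retention in care "will be defined as the proportion of patients retained in ART care at Ubuntu Clinic, in or out of an AC". This wording does not refer to missed visits.
- **Schedules.** Standard of care (SOC) clubs "meet five times per year (bi-monthly with a four-month gap over the end of the year to support migration patterns". In the other arm, "The Intervention ACs meet twice annually receiving six-month ART refills", and each member is asked to "individually attend a third visit for routine blood collection anytime two-four weeks before their annual clinical assessment AC visit". In SOC only, "Patients are allowed to send a treatment “buddy” to collect their ART refill to every alternate AC".
- **Data window (Data collection).** 24 months from study start, plus three months to settle final outcomes, so 27 in all.
- **Interim (Interim analyses; Timelines).** "12-month primary outcomes will be assessed", and the Data Monitoring Committee reviews them in March 2019. Study design states that the comparison is one of non-inferiority.

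**The concern.** An absence can start the loss clock only when a visit falls due. An SOC member who stops attending normally misses a visit within two months, or four over the year-end. An intervention member who stops just after collecting may have no club visit to miss for six months. The same behaviour therefore reaches the definition at different times, and a temporary absence has a different chance of reaching it at all.

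In a non-inferiority trial, under-recording loss in the intervention arm is the unsafe direction: it can make the new schedule look better than it is. The outputs exposed are the Kaplan-Meier curves, the hazard ratios, and any 12-month status that requires the three months to have already run.

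**Working it through.** **Inputs from the article.** The loss rule, both schedules and the 27-month close are as above. Sample size section: 993 per arm, cluster size 24, intracluster correlation 0.05 to 0.10, retention 75 to 85%, a 10-point difference, one-sided alpha 0.025.

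**Assumptions.** The same constant disengagement hazard in both arms, set by 24-month retention S. SOC visits at months 4, 6, 8, 10, 12, 16, 18, 20, 22, 24 (placing the long gap later in the year changes nothing material). Intervention club visits at 6, 12, 18, 24. Blood visits, where counted, at 11.25 and 23.25.

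**1. The plan's own figures.** Design effect 1 + 23 × ICC = 2.15 and 3.30; effective n per arm 993/2.15 = 461.9 and 993/3.30 = 300.9. Reading the 10 points as the margin, power = Φ(0.10/√(2p(1−p)/n) − 1.96). This gives 0.809 (75%, 3.30) to 0.989 (85%, 2.15), against 0.80 to 0.98 stated. The 10 points can therefore serve as a yardstick. The article gives no figure for ascertainment of loss by arm.

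**2. Delay until the rule is met** (mean wait for the next visit, plus 3 months).
- SOC: (8/12) × 1 + (4/12) × 2 = 1.33, so 4.33 months; maximum 4 + 3 = 7.
- Intervention, club visits only: 3 + 3 = 6.0 months; maximum 9.
- Intervention, blood visit counted: (6² + 5.25² + 0.75²)/(2 × 12) = 2.67, so 5.67 months.
- Difference: 1.3 to 1.7 months.

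**3. Recorded loss when the three months must have elapsed by the landmark.** The missed visit must fall by month 9 (or 21). SOC then captures disengagement in the first 8 (20) months, the intervention arm in the first 6 (18). Recorded loss = 1 − S^(k/24).

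| S | 12 months, SOC v intervention | 24 months, SOC v intervention |
|---|---|---|
| 0.75 | 9.1% v 6.9% (2.2 points) | 21.3% v 19.4% (1.9) |
| 0.80 | 7.2% v 5.4% (1.7) | 17.0% v 15.4% (1.6) |
| 0.85 | 5.3% v 4.0% (1.3) | 12.7% v 11.5% (1.2) |

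The spurious rate ratio is about 6/8 = 0.75 at 12 months and 18/20 = 0.90 at 24.

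**4. Effect of the event date** (24-month events over person-time, true ratio 1, by simulation).
- Missed visit + 3 months: 0.90.
- Missed visit: 0.98 to 0.99.
- Last attended visit: 1.01 to 1.02.

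**5. Temporary absences.** A gap of g months counts if the wait for the next visit is at most g − 3. With starts uniform over months 0 to 18 there are seven SOC intervals and three intervention intervals (club visits only).
- 4 months: 7/18 = 39% v 3/18 = 17%.
- 5 months: 14/18 = 78% v 6/18 = 33%.
- 6 months: 16/18 = 89% v 9/18 = 50%.
- 8 months: 100% v 15/18 = 83%.
- 9 months: 100% in both.

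**6. Effect of the 27-month close.** A missed month-24 visit plus 3 months is month 27. Permanent loss before month 24 is then recorded equally: 25, 20 or 15% in each arm, difference 0. There is no slack. If the month-24 visit falls just outside and bloods are not counted, capture runs to month 22 v 18. Then 1 − S^(22/24) v 1 − S^(18/24) gives 23.2 v 19.4% at S = 0.75 and 13.8 v 11.5% at 0.85, a gap of 2.4 to 3.8 points. Counting the month-23 blood visit closes or slightly reverses it.

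**7. A common contact window.** With any contact in months 9 to 15, an SOC member seen at month 10 and then gone still counts as retained. Recorded loss is 1 − S^(10/24) v 1 − S^(12/24): 11.3 v 13.4% at S = 0.75 and 6.6 v 7.8% at 0.85. In months 21 to 27 it is 23.2 v 25.0% and 13.8 v 15.0%. The residual is 1.2 to 2.1 points against the intervention, and less if blood visits count as contact.

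**The case against.** The strongest reply is that the plan already contains most of the remedy. The primary outcomes are retention, viral load completion and suppression, and power rests on a difference in retention proportions. Retention is not worded by missed visits, and nothing says that non-inferiority will be judged on a hazard ratio. The three extra months match the loss window exactly. First supply in October/November 2017 and review in March 2019 leave time for a three-month look-forward from month 12. All of this stands, with two limits. No rule says that the look-forward is used at 12 months. Timelines also lists data collection as October 2017 to September 2019 while placing its completion in early 2020, so the extra months are less secure than Data collection suggests.

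A second reply is that someone holding a six-month refill is not yet overdue, so part of the difference is real treatment cover. That is reasonable, but the stated definition concerns return to care, not drug cover.

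A third is that the article is abridged and the loss date may be fixed elsewhere. That is fair for the date; the missed-visit trigger, however, is stated here.

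A reader might infer that the rule always favours the intervention. The documents do not support this. Last-attendance dating reverses the ratio slightly. SOC buddy collection can hide absence. The intervention blood visit is an extra scheduled contact. Unrecognised loss stays in the viral load completion denominator, which works against the intervention.

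**Conclusion.** The point holds for time to loss, its hazard ratios and the counting of temporary absences. With equal disengagement, the rule is met 1.3 to 1.7 months later in the intervention arm. Dated at missed visit plus three months, the false advantage is 1.2 to 1.9 points at 24 months, and 1.3 to 2.2 points at 12 months if no look-forward is used. Against a 10-point difference this is modest, but it is systematic and comes from the definition itself.

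A reader might also infer that the final retention comparison is biased, or that the interim review must be. Neither follows. For permanent loss the 24-month proportion is largely protected, provided the month-24 visit falls inside the 27-month close, and the March 2019 date allows the same protection at 12 months. This is a correction worth making before analysis, not a flaw that invalidates the trial.

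The sizes rest on a constant and equal hazard, the assumed visit months, and reading the 10 points as the margin.

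**What to change.** 1. Base the non-inferiority conclusion on retention proportions at 12 and 24 months, using one contact-based rule in both arms: any attendance, dispensing or laboratory record within a common window.
2. Set that window from the actual calendar so that it contains a scheduled visit in each arm, for example months 9 to 15 and 21 to 27. A window of 24 to 27 is risky: Timelines puts the second six-month supply in March/April 2018, about month 5 to 6, so a later intervention visit could fall just before month 24 and retained members be called lost. Keep the window as narrow as the calendar permits, because SOC has more visits inside any wide one. The residual in step 7 leans against the intervention, which is the cautious direction here, and should be acknowledged.
3. Apply the same three-month look-forward at the 12-month interim as at 24 months.
4. State the date that loss carries, whether the blood visit can trigger it, and whether a buddy's collection counts as contact.
5. Do not infer non-inferiority from the visit-triggered hazard ratio. Treat the time-to-loss curves as descriptive, or analyse loss as interval-censored between last contact and first missed contact.

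The cost is small: some redefinition and analysis work, and a hazard ratio with less inferential weight. Data collection already provides for extracting visit, dispensing and laboratory data.

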### Study design

This is a cluster-randomized control trial to evaluate whether patients in Intervention ACs have non-inferior retention and viral load assessment and viral suppression outcomes compared to those in SOC ACs.

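### Suppression and viral load completion are compared only in post-randomisation subsets, and no primary outcome adds up losses from care, missed tests and viraemia over all randomised participants

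*Protocol article*

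**What the plan says.** The Study design section asks whether patients in the intervention clubs "have non-inferior retention and viral load assessment and viral suppression outcomes compared to those in SOC ACs". Primary outcome measures lists four outcomes: retention in clinic care, retention in club care, viral load completion and viral suppression.

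Data analysis, Primary outcomes, sets the denominators:

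- **Suppression:** "Only those patients with a completed viral load and retained in care at 24 months, are included in the denominator for viral load suppression".
- **Completion** (a viral load drawn in each 12-month period): "If a patient is lost to follow-up, transferred out of clinic, or dies they are excluded from the denominator".
- **Retention in clinic care:** only transfers out of the clinic leave the denominator, so a participant lost to follow-up counts as not retained.
- **Retention in club care:** those who transfer out of their club leave the denominator.

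The description of the two arms and Table 2 show that they differ in ways that bear on attendance and testing. The intervention has two club visits a year against five, no treatment buddy, and blood drawn at a separate individual visit instead of a club visit.

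**The concern.** Being retained and being tested both happen after randomisation, and the intervention may change both. A comparison limited to those who stayed and were tested is not a comparison of the randomised clubs. Those removed have stopped attending or have no result, and some of them are plausibly off treatment. If the intervention arm loses more of them, the suppression comparison does not register it, and a loss from care does not register in completion either.

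At stake is a statement that six-month refills give non-inferior suppression when fewer of the participants randomised to them are known to be suppressed at 24 months. The denominators are stated rules, so this is not a detail that the article merely leaves to a fuller document.

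**Working it through.** **Design inputs** (Sample size and power considerations)

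- 993 participants per arm. The plan "assumed a correlation ranging from 0.05–0.10 and an average cluster size of 24".
- On error control, "all statistical tests were one-tailed with an alpha of 0.025 to address type 1 error".
- Retention of 75% to 85%, and a 10-point difference.

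**Reproducing the plan's power**

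- Design effect = 1 + (24 − 1) × ICC = 2.15 at ICC 0.05 and 3.30 at ICC 0.10, as stated.
- Effective n per arm = 993/2.15 = 461.9 and 993/3.30 = 300.9.
- Non-inferiority power with no true difference and a 10-point margin = Φ(0.10/√(2p(1−p)/n) − 1.96).
- p = 0.75, n = 300.9: Φ(0.10/0.0353 − 1.96) = 0.81. p = 0.85, n = 461.9: Φ(0.10/0.0235 − 1.96) = 0.99.

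The plan states 0.80 to 0.98. This agreement supports reading the 10-point difference as the margin for retention. Treating 85% vs 75% as a difference to detect gives 0.87 to 0.97, a poorer match.

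**Assumptions not in the article:** the testing rate among those retained, the suppression rate among those tested, and the use of a 10-point margin for every outcome. One testing rate stands for both 12-month periods, transfers and deaths are set aside, and the same design effect is applied to the subsets.

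**Formulas**, with r = retained, t = tested if retained, s = suppressed if tested:

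- suppression as defined = s; completion as defined = t
- suppression in all randomised = r × t × s; completion with losses as failures = r × t
- chance of declaring non-inferiority = Φ((0.10 − deficit)/SE − 1.96), with unpooled SE. Effective n is multiplied by r for completion and by r × t for suppression as defined.

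**Three cases**, s = 95% in both arms. Differences are intervention minus control, in points; brackets give the chance of declaring non-inferiority at ICC 0.10 to 0.05.

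| Case | Retention | Completion as defined | Suppression as defined | Suppression, all randomised |
|---|---|---|---|---|
| (a) r 85 vs 75, t 90 both | −10 (0.03) | 0 (0.95–0.99) | 0 (1.00) | 72.7% vs 64.1%: −8.6 (0.06–0.07) |
| (b) r 85 both, t 90 vs 80 | 0 (0.93–0.99) | −10 (0.03) | 0 (1.00) | 72.7% vs 64.6%: −8.1 (0.07–0.09) |
| (c) r 85 vs 80, t 90 vs 85 | −5 (0.37–0.52) | −5 (0.39–0.55) | 0 (1.00) | 72.7% vs 64.6%: −8.1 (0.07–0.09) |

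For case (c): 0.85 × 0.90 × 0.95 = 0.727 and 0.80 × 0.85 × 0.95 = 0.646. With losses counted as not completed, completion is 0.765 vs 0.680, or −8.5 points.

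**Range for case (c).** With retention 85 vs 80 and a 5-point testing gap:

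- testing 80 vs 75, s = 90%: 0.90 × (0.85 × 0.80 − 0.80 × 0.75) = 7.2 points
- testing 95 vs 90, s = 98%: 0.98 × (0.85 × 0.95 − 0.80 × 0.90) = 8.6 points

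Suppression as defined differs by 0 whenever s is equal in the two arms.

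**The case against.** The strongest reply is that the outcomes form a cascade, with each loss scored at its own step. Clinic retention is primary, is the outcome the trial is powered on, and counts losses as failures. Completion is primary and counts a missed test in a retained participant as a failure, so a harmful effect of the separate blood visit would show there. Study design also joins the outcomes with the word *and*. All of this stands. A reader might infer that worse retention or testing cannot count against the intervention at all. Cases (a) and (b) show otherwise: a 10-point deficit at one step passes that step's own test with a chance of only about 0.03.

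The cascade does not cover deficits spread over two steps. In case (c), if retention and completion were independent and both were required, both would pass in about 0.37 × 0.39 = 14% to 0.52 × 0.55 = 29% of trials. The article states no formal rule that every primary outcome must succeed, so suppression might also be claimed alone.

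A reader might also infer that excluding losses always pulls a difference toward zero. It does not. It hides a difference only when losses or missed tests differ by arm, and an all-randomised outcome has its own weakness. With 85% retained and 90% tested in both arms (assumed), true suppression of 95% vs 85% among those tested shows 10 points as defined but 0.85 × 0.90 × 10 = 7.65 points over all randomised. That is a good reason to keep the conditional proportion.

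Two further safeguards are real but partial. The planned Kaplan-Meier estimate of time to first unsuppressed viral load can capture viraemia recorded before a participant leaves. Participants referred back to clinic care after rebound stay in the suppression denominator. Neither captures a participant who leaves without a result.

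Finally, the article is an abridged protocol, and an all-randomised analysis may exist in documents not shown. Its absence is therefore not the criticism; the stated primary denominators are.

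**Conclusion.** The point holds in a limited form. Two of the four primary outcomes compare subsets selected after randomisation: suppression is blind to losses and to missed tests, and completion is blind to losses. The trial as a whole is not blind to them, because a large deficit in retention or in testing would appear in its own primary outcome. What the article lacks is an outcome that adds the steps together. Moderate deficits at two steps (85% vs 80% retained, 90% vs 85% tested) leave suppression as defined at 0 difference and lower suppression among all randomised by 8.1 points, or by 7.2 to 8.6 over the rates tried.

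The zero follows from the definition and needs only equal suppression among those tested. The size of the hidden deficit depends on assumed testing and suppression rates. The chances of passing also depend on applying a 10-point margin to outcomes for which the article gives none.

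**What to change.** 1. Add a primary-level outcome beside the conditional one: the proportion of all participants in randomised clubs with a viral load below 400 copies/mL in the second 12-month period. Lost, dead or no result counts as not suppressed. For those who transferred, use the linked provincial laboratory results.
2. Keep participants lost to follow-up in the completion denominator, as not completed.
3. Conclude non-inferior suppression only if both the all-randomised and the conditional comparisons support it.
4. Show the components by arm: retained, tested if retained, suppressed if tested, and no result found.

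**Cost.** The change needs new definition wording and a little linkage work, since Data collection already plans laboratory extraction and linked provincial data. Headline percentages fall, and the composite mixes non-retention with viraemia and can dilute a pure viraemia difference.

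Power also falls. With the arms truly equal, 90% tested, 95% suppressed and a 10-point margin (all assumed), the power formula above gives 0.79 to 0.93 for the all-randomised outcome at 85% retention (p = 0.727), and 0.72 to 0.89 at 75% retention (p = 0.75 × 0.90 × 0.95 = 0.641), for ICC 0.10 to 0.05.

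**Timing.** Timelines places the interim analysis in March 2019 and the final 24-month analysis after data collection ends. The change should be dated before that final analysis and decided by people who have not seen interim results by arm.
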